### Data collection and management

2.5

As shown in **Table 1**, medical history and demographic information were collected during the screening phase. In addition, urine or blood pregnancy tests (for females only), physical examinations, vital signs, height, weight, waist circumference, 12-lead electrocardiogram (ECG), routine blood test, routine urine test, blood biochemistry, adverse events, HbA1c, fasting blood glucose, fasting insulin + C-peptide, postprandial 2h blood glucose, and postprandial 2h insulin + C-peptide levels will be assessed, and concomitant medications (antidiabetic and other drugs) will be recorded.

**Table 1 T1:** Schedule of activities.

Study period	Screening period	Treatment period			
Visit day¹	V0	V1^2^	V2	V3 (end of treatment)	V4 (Follow-up)
Study week	≤2 weeks	Baseline	12w ± 5d	24w ± 5d	End of treatment+7d ± 3d
Sign informed consent forms^3^	X				
Eligibility (inclusion/exclusion criteria)	X	X			
Demographic	X				
Family history of diabetes	X				
History of diabetes and complications	X				
Medical/Current conditions	X			X	
Treatment					
Randomization		X			
Drug dispensation and accountability		X	X	X	
Safety assessments					
Pregnancy test (urine/blood, females only)	X	X	X	X	
Physical examination	X	X	X	X	
Vital signs (blood pressure, heart rate)	X	X	X	X	
Height	X				
Body weight	X	X	X	X	
Waist circumference		X	X	X	
12-lead electrocardiogram	X	X	X	X	
Hematology^4^	X	X	X	X	
Urinalysis^5^ (urine routine + urea albumin creatinine ratio)	X	X	X	X	
Biochemistry^6^	X	X	X	X	
Adverse events	X	X	X	X	X
Efficacy assessments					
Glycated hemoglobin ^7^	X	X	X	X	
Fasting plasma glucose (oral glucose tolerance test + C-peptide release test + insulin release test)	X	X	X	X	
2hr-plasma glucose^8^ (oral glucose tolerance test + C-peptide release test + insulin release test)	X	X	X	X	
Fasting insulin + c-peptide (oral glucose tolerance test + C-peptide release test + insulin release test)	X	X	X	X	
2hr-insulin, c-peptide^8^ (oral glucose tolerance test + C-peptide release test + insulin release test)	X	X	X	X	
Fasting plasma glucose (fingertip blood, in hospital)			X	X	
2h-plasma glucose (fingertip blood, in hospital)			X	X	
Continuous glucose monitoring index (time in tight target range\time in range\time above range\time below rang)			X		
Other assessments					
Concomitant glucose lowering medication collection	X	X	X	X	X
Concomitant other medication collection	X	X	X	X	X
Questionnaire					
Diabetes quality of life		X	X	X	
Diabetes treatment satisfaction questionnaire			X	X	
Adherence to refills and medication scale for diabetes			X	X	

^1^Visit Day: Visits will be conducted by phone at V4 for safety follow-up; patients should return to the hospital at V1 (baseline), V2 (12 weeks), and V3 (24 weeks).

^2^V1 (Baseline): If the date of blood test (including Hematology, Biochemistry, HbA1c, Fasting blood glucose, 2hr-plasma glucose, fasting insulin+c-peptide, 2hr-insulin+c-peptide) and Urinalysis at V0 is ≤ 2 weeks from V1, there is no need to be repeated at V1, and other tests except for that will still have to be performed at V1.

^3^Signing of ICF(s): Patients will be required to sign the ICF for the main study and the CGM sub-study.

^4^Hematological test:Absolute neutrophil count, Hemoglobin, Total white cell count, Absolute lymphocyte count, Platelet count

^5^Urinalysis: Urine routine, urine albumin-to-creatinine ratio (UACR).

^6^Biochemistry: Aspartate transaminase (AST), alanine transaminase (ALT), Albumin, Creatinine (Cr), Total Bilirubin, Blood urea nitrogen (BUN)/blood urea (urea), creatine phosphokinase (CPK), high-density lipoprotein cholesterol (HDL-C), low-density lipoprotein cholesterol (LDL-C), total cholesterol (TC), and triglycerides (TG).

^7^HbA1c will be tested in a local laboratory during the screening period. HbA1c will be tested in the central laboratory during the pre-randomization visit and treatment period. The HbA1c level will be tested by the central laboratory at V1, and the results will be obtained within 2 weeks. Eligible patients will be randomized according to the test results.

^8^2hr-plasma glucose/2hr-insulin, c-peptide: The time window for blood sampling is ±10min.

During the treatment period, patients will visit the hospital for follow-up at weeks 0, 12 (± 5 days), and 24 (± 5 days). The follow-up will include medication dispensing and management, urine or blood pregnancy test (for females only), physical examinations, vital signs, weight, waist circumference, 12-lead ECG, blood routine test, urine routine test, blood biochemistry, adverse events, HbA1c, fasting blood glucose, fasting insulin + C-peptide, postprandial 2h blood glucose, postprandial 2h insulin + C-peptide levels, and recording of concomitant medications (antidiabetic and other drugs). At weeks 12 (± 5 days) and 24 (± 5 days), fasting fingertip blood glucose and postprandial 2h fingertip blood glucose levels were measured. At week 12 (± 5 days), CGM was performed for approximately five days. One week (± 3 days) after the end of treatment, a telephonic follow-up will be conducted to record adverse events and concomitant medications (antidiabetic and other drugs).

Patient satisfaction, quality of life, and adherence were evaluated using DTSQ, DQOL questionnaire, and ARMS-D. The patients completed the DQOL questionnaire at week 0 and the DTSQ, DQOL questionnaire, and ARMS-D at weeks 12 and 24.

All patient data related to the study will be recorded on case report forms (CRFs), unless electronically transmitted to AstraZeneca or a designee (e.g., central laboratory). The investigator must maintain an accurate documentation (source data) to support the information entered in each CRF. The investigator must allow for monitoring, auditing, Institutional Review Board (IRB)/Independent Ethics Committee (IEC) review, and regulatory agency inspections related to the study, thereby providing direct access to source data files. Records and documents related to this study, including signed informed consent forms (ICFs), must be retained by the investigator for at least 25 years after study completion or as required by local regulations. Each subject was assigned a unique identifier to ensure privacy of the included participants. The data transmitted will not include the participant’s name or any personally identifiable information; only identifiers to distinguish the subjects will be used.

### Sample size

2.6

The primary objective of this study was to demonstrate the non-inferiority of the FDC regimen of dapagliflozin/metformin XR to co-administered dual therapy of dapagliflozin and metformin for changes from baseline to week 24 in HbA1c within a non-inferiority margin of 0.30%, assuming a standard deviation of 1.2% (24). At a 1-sided significance level of 0.025, 253 patients per arm will be needed to provide 80% power (given a true difference of zero between the FDC regimen of dapagliflozin/metformin and XR and co-administered dual therapy of dapagliflozin and metformin). Assuming a dropout rate of 20%, 632 patients were randomized.

For the CGM sub-study, though exploratory in nature, the sample size was calculated based on exploratory hypothesis testing of the primary exploratory endpoint, which is the proportion of TITR (3.9-7.8 mmol/L) at week 12. Assuming a mean difference of 10%, standard deviation of 30%, and 2-sided significance level of 0.05, 143 patients per arm will provide 80% power for exploratory superiority testing. Assuming a dropout rate of 20%, approximately 358 patients were needed for the sub-study.

### Statistical analysis

2.7

The full analysis set (FAS) included all randomized patients with documented baseline assessment and at least one post-baseline assessment for the primary efficacy endpoint. The per-protocol analysis set (PPS) will include patients without an important protocol deviation that might affect the primary efficacy analyses. The CGM analysis set will include patients from the full analysis set administered at least one dose of the study treatment prior to CGM performance, as well as CGM-evaluable data. The safety analysis set (SS) included all randomized patients who were administered at least one dose of the study treatment.

Primary efficacy analysis will be performed on the PPS, excluding HbA1c measurements after receiving rescue medications or permanent discontinuation of the study intervention. Missing data at week 24 will be handled using the multiple-imputation approach. Analysis of covariance (ANCOVA) will be used for the primary analysis. Point estimates and 2-sided 95% confidence intervals for the mean change within each treatment group, as well as the difference in mean change between the two groups, will be provided. The dapagliflozin/metformin FDC regimen was considered non-inferior to dapagliflozin and metformin co-administered if the upper limit of the 2-sided 95% (or 1-sided 97.5%) confidence interval of the difference in mean change in HbA1c from baseline to week 24 between the groups was below 0.3%.

The secondary endpoints will be analyzed in the PPS. An ANCOVA model will be used to analyze the absolute changes in FPG and PPG from baseline to week 24, reporting the point estimates of the average changes and two-sided 95% confidence intervals (CIs) within each treatment group as well as the differences in mean changes between groups. The difference in the proportion of patients achieving HbA1c levels below 7.0% at week 24 will be analyzed using logistic regression, adjusting for baseline HbA1c values. Participants with missing HbA1c measurements at week 24 will have the values imputed by dichotomizing the imputed HbA1c values at week 24. Odds ratios (ORs) and 95% confidence intervals will be reported. Descriptive statistics will be used for DQOL, DTSQ, and ARMS-D scores. An ANCOVA model will analyze the changes in the DQOL score from baseline to weeks 12 and 24. Point estimates of mean changes and 95% CIs within each group were calculated along with the differences in mean changes between the two groups. Differences in DTSQ and ARMS-D scores at week 24 between the two groups will be compared using the t-test or Wilcoxon rank-sum test, based on the normality and homogeneity of variances of the data.

The analyses for the primary and secondary endpoints will be repeated using FAS to examine the robustness of the results.

Exploratory endpoints will be analyzed based on the CGM analysis set. Point estimates and 95% CIs for all exploratory outcomes within each group were calculated along with estimates and 95% CIs for the differences between the two groups.

Safety analysis will be based on SS, summarizing the numbers and incidence rates of AEs, SAEs, and ADRs in each treatment group. At each scheduled time point, descriptive statistics will be used to summarize the values and changes from the baseline in vital signs, physical examinations, and clinical laboratory parameters within the different groups.

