Glycemic control in patients with diabetes typically requires combination therapies. Studies have shown that initial combination therapy could achieve faster glycemic control and maintain its effects for a longer duration than sequential add‐on therapy (14, 15). The American Diabetes Association (ADA) 2025 Standards of Medical Care in Diabetes and Guidelines for the Prevention and Treatment of Diabetes Mellitus in China (2024 edition) recommended considering initial combination therapy, including fixed-dose combination (FDC), for patients whose glycated hemoglobin (HbA1c) is over 1.5% above the target level (2, 16). Furthermore, combination therapy was recommended for T2DM patients with the HbA1c ≥7.5%, according to the American Association of Clinical Endocrinology (AACE) Consensus Statement (2023) and Metabolic Disease Management Guideline for National Metabolic Management Center (MMC) (17, 18). Nowadays, low adherence to diabetes medication remains an ongoing problem (19). Studies have shown that medication adherence is inversely related to the number of medications (20), and compared to using separate drugs, fixed-dose combination therapy may significantly improve patient adherence to treatment (21). XIGDUO^®^ XR tablet is a FDC of dapagliflozin and metformin hydrochloride XR tablets, and studies have shown bioequivalence between FDC and co-administered dapagliflozin and metformin XR tablets (22). However, it remains uncertain whether the efficacy of dapagliflozin/metformin FDC is comparable to that of co-administration.

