### Randomization and study interventions

2.4

Patients were centrally randomized (1:1) to one of the two treatment groups using an Interactive Response Technology/Randomization and Trial Supply Management (IRT/RTSM). Prior to the study initiation, contact information and login directions for the system were provided to each site. Following randomization, patients in the FDC group received a single tablet containing 10 mg of dapagliflozin and 1000 mg of metformin hydrochloride XR once daily. Patients in the co-administration group received one tablet of 10 mg dapagliflozin once daily, and metformin hydrochloride XR, administered as two 500 mg tablets once daily with meals, or as one 500 mg tablet twice daily with meals if the patient is intolerant to the two-tablet dose. This study did not involve dose adjustments for study medications. The duration of treatment was 24 weeks.

The rescue treatment criteria from week 4 to week 12 were based on an FPG level exceeding 13.32 mmol/L, confirmed by a second measurement 3–5 days later. The rescue treatment criteria from weeks 12 to 24 were based on an FPG level exceeding 11.10 mmol/L (23). Rescue medications include but are not limited to metformin, GLP-1 receptor agonists, DPP-4 inhibitors, thiazolidinediones, sulfonylureas, and insulin. Patients administered rescue medications will continue to participate in the study and the results will be independently analyzed.

Subjects had to discontinue the use of prescription or over-the-counter medications (including vitamins, recreational drugs, dietary supplements, or herbal supplements) 7 days prior to the start of the study intervention (or 14 days in case the medication is a potential enzyme inducer) or 5 half-lives of the medication (whichever is longer) until the end of follow-up, unless the investigator and sponsor believe the medication will not interfere with the study. Acetaminophen/paracetamol with a dosage of ≤2 g/day was allowed at any time during the study period.

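### Non-inferiority is decided on the per-protocol set alone, with HbA1c after stopping deleted, so a deficit from differential stopping can stay out of the decision

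*Protocol article*

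**What the plan says.** The Statistical analysis section (2.7) fixes the primary analysis: "Primary efficacy analysis will be performed on the PPS, excluding HbA1c measurements after receiving rescue medications or permanent discontinuation of the study intervention". It adds: "Missing data at week 24 will be handled using the multiple-imputation approach". The test is ANCOVA, and the single success criterion is an upper limit of the two-sided 95% confidence interval below 0.3%.

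The PPS is defined thus: "The per-protocol analysis set (PPS) will include patients without an important protocol deviation that might affect the primary efficacy analyses". The deviations are not listed. The FAS consists of "all randomized patients with documented baseline assessment and at least one post-baseline assessment for the primary efficacy endpoint". Its role is given in one sentence: "The analyses for the primary and secondary endpoints will be repeated using FAS to examine the robustness of the results". Nothing makes the conclusion depend on that repeat.

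Two other places bear on the point. The Introduction says that "studies have shown bioequivalence between FDC and co-administered dapagliflozin and metformin XR tablets" and presents comparability of efficacy as the open question. Randomization and study interventions (2.4) lets the co-administration arm take metformin XR as two tablets at once, "or as one 500 mg tablet twice daily with meals if the patient is intolerant to the two-tablet dose", and describes no counterpart for the FDC arm. On rescue, the same section says: "Patients administered rescue medications will continue to participate in the study and the results will be independently analyzed".

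**The concern.** Both arms receive the same daily doses, and bioequivalence is taken as established. An HbA1c difference would then be expected to arise mainly through adherence, tolerability and stopping. The decision rule sets aside what happens after permanent discontinuation and replaces it with imputed values. If the imputation draws on patients still on treatment, a stopper is scored as though treatment had continued. If stopping were commoner on FDC, the resulting loss of control would not enter the decision.

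Two features make this more than theoretical. Only one arm has a described alternative for metformin intolerance, so stopping may differ by arm. The trial is also open-label, so knowledge of the arm can influence who stops and who is classed as a deviator. A comparison restricted on such grounds no longer has the protection of randomisation, and the bias could run either way. At stake is whether a positive result answers the efficacy question posed in the Introduction or only a narrower question about treatment while taken.

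**Working it through.** **Inputs from the protocol article.** Margin 0.30, SD 1.2, one-sided 0.025, true difference 0, 253 per arm, 20% dropout, 632 randomised 1:1 (316 per arm).

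**Assumed inputs, not in the document.** Stopping proportions pF (FDC) and pC (co-administration); HbA1c loss L after stopping; stopping unrelated to response so far; no on-treatment difference; deleted values imputed as if on treatment.

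**1. The plan's own figure.** n = 2 × 1.2² × (1.96 + 0.8416)² / 0.30² = 251.2 per arm. With the t distribution, power is 79.98% at 252 and 80.14% at 253, so 253 is correct. Then 506 / 0.8 = 632.5, against 632 stated. The sample size reproduces.

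**2. On-treatment analysis.** SE = 1.2 × √[1/(316(1 − pF)) + 1/(316(1 − pC))], and P(declare) = Φ(0.30/SE − 1.96). For 25% vs 15%, SE = 0.1069 and P = Φ(0.845) = 0.80. For 30% vs 10%, SE = 0.1076 and P = Φ(0.829) = 0.80. L does not appear: this analysis does not respond to what stopping costs.

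**3. As-randomised analysis keeping values after stopping.** True difference d = (pF − pC) × L. Variance per arm = 1.44 + L² × p(1 − p). SE = √[(vF + vC)/316], and P = Φ((0.30 − d)/SE − 1.96).

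| Stopping (FDC vs co-administration) | L | d | vF, vC | SE | P as randomised | P on treatment |
|---|---|---|---|---|---|---|
| 25% vs 15% | 1.0 | 0.10 | 1.6275, 1.5675 | 0.1006 | 0.51 | 0.80 |
| 25% vs 15% | 1.5 | 0.15 | 1.8619, 1.7269 | 0.1066 | 0.29 | 0.80 |
| 30% vs 10% | 1.5 | 0.30 | 1.9125, 1.6425 | 0.1061 | 0.025 | 0.80 |

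Simulation agrees (about 52%, 30% and 2.6% as randomised). A version with regression imputation by arm from baseline and week 12, followed by ANCOVA, gives for the last row a mean estimate of 0.00 and non-inferiority in 81% of runs with deletion, against 0.30 and 2% with the values kept.

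**4. How extreme must stopping be?** A deficit of 0.30 from stopping alone needs an excess on FDC of 0.30/L: 20 percentage points at L = 1.5, 30 at L = 1.0, 40 at L = 0.75. That is large against a planned 20% dropout.

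**5. Rescue behaves differently.** Assume 20% (FDC) vs 5% fail on drug by 2.0 points, an on-drug deficit of 0.15 × 2.0 = 0.30, and that rescue restores control. Keeping post-rescue values gives an estimate near 0.00 and non-inferiority in 85% to 87% of runs. Deleting and imputing gives 12% if every rescue follows the week-12 sample, 42% if half do, and 82% if all precede it. Deletion is therefore usually the more cautious choice, except for rescue before week 12, when no post-baseline HbA1c is available to inform the imputation.

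**6. Power if both analyses must succeed.** With 20% stopping in both arms and a loss of 1.0 to 1.2 points, the on-treatment leg has about 80% power and the as-randomised leg about 85% to 83%. Simulated joint power is 75.4% to 76.2%.

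**The case against.** The strongest reply is that the plan targets the effect while on treatment and without rescue. For that target, with data missing at random, a zero difference is the right answer, and declaring non-inferiority is no error. This stands as far as it goes: the stated analysis is coherent for that question. It does not follow that this question alone should settle a trial whose stated uncertainty is comparability of efficacy.

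Several stronger readings are tempting, and the document does not support them.

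- A reader might infer that a deficit cannot show at all. Week-12 HbA1c can carry part of it into the imputation, a FAS repeat is planned, and rescued patients' results are analysed separately.
- A reader might infer that deleting post-rescue values favours FDC. Step 5 shows that the opposite is usually so.
- A reader might infer that the PPS removes every stopped, rescued or poorly adherent patient. Its definition names none of them. If poor adherence counts as a deviation and is commoner with separate tablets, exclusion could work against FDC.
- A reader might infer that no as-randomised analysis exists. The article condenses a fuller protocol, and an analysis plan that is not shown may hold sensitivity analyses. That the FAS repeat carries the same deletions is the natural reading, but it is not stated.

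It is also fair to say that no section states that HbA1c is collected after permanent discontinuation. None of this alters the stated success rule, which rests on one analysis set and one treatment of stopping.

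**Conclusion.** The concern holds for stopping and for the decision rule. One PPS analysis decides the claim, values after discontinuation are replaced by imputation, and the FAS result cannot change the conclusion. A deficit from differential stopping can therefore be hidden from the decision, and the direction of PPS bias is unknown.

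With moderate assumed imbalance (25% vs 15%, loss 1.0 to 1.5), the chance of declaring non-inferiority is about 80% under the on-treatment analysis, against 51% to 29% as randomised. The true difference there is 0.10 to 0.15, inside the margin, so these are not false declarations; they show how little the rule responds to stopping. Calling the claim false is warranted only for the as-randomised question and a true deficit at or beyond 0.30, which takes inputs as extreme as 30% vs 10% stopping with a 1.5-point loss (about 80% vs 2.6%). All stopping rates and losses are assumptions, as is imputation on on-treatment lines. The point does not extend to the exclusion of post-rescue values, which is defensible.

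**What to change.** Change the decision rule. Claim non-inferiority only if the upper 95% limit is below 0.3% in both (a) the PPS analysis as planned and (b) a FAS analysis by randomised arm that keeps HbA1c observed after treatment discontinuation, with multiple imputation for stoppers only where the value was not collected.

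Treat rescue as a separate matter. The exclusion of post-rescue HbA1c may stay, with an analysis that keeps those values as a sensitivity analysis, since keeping them can mask a deficit. Say what the separate analysis of rescued patients is for.

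State that the scheduled week-24 HbA1c is still taken from patients who stop treatment, and restate the power of the joint rule.

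The cost is wording, one further analysis and continued data collection after stopping. At 632 randomised, joint power is about 76% rather than 80% under the plan's assumptions with 20% stopping in both arms. If HbA1c after stopping is not collected, leg (b) falls back on imputation for the very patients at issue and protects less. The FAS also omits randomised patients with no post-baseline HbA1c, which is a further reason to keep stoppers in follow-up.

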### Endpoints

2.3

The primary endpoint of the study was the change in HbA1c level from baseline after 24 weeks of treatment. The secondary endpoints included the following: (1) The proportion of patients achieving HbA1c below 7.0%, absolute change in fasting plasma glucose/postprandial glucose (FPG/PPG) from baseline to week 24, and (2) the difference in satisfaction scores between the two groups measured using the diabetes treatment satisfaction questionnaire (DTSQ) at week 24. (3) Change from baseline in the diabetes quality of life (DQOL) questionnaire scores at weeks 12 and 24. (4) The differences in patient medication usage between the two groups were measured with adherence to refills and medications scale for diabetes (ARMS-D) at week 24. (5) Adverse events (AE), serious adverse events (SAE), and adverse drug reactions (ADRs). (6) Vital signs. (7) Physical examination. (8) Clinical laboratory indices. (9) Electrocardiogram

In the exploratory substudy, the primary exploratory endpoint was the proportion of time in the tight target range (TITR, 3.9-7.8 mmol/L). Secondary exploratory endpoints included time in range (TIR, i.e., the percentage of readings and time that a person spends with their blood glucose levels in a target range of 3.9–10 mmol/L), time below range (TBR, i.e., the percentage of readings and time that a person spends with their blood glucose levels below the target range), time above range (TAR, i.e., the percentage of readings and time that a person spends with their blood glucose levels above the target range), mean amplitude of glycemic excursions (MAGE, the mean blood glucose values exceeding one standard deviation (SD) from the 24‐hour mean blood glucose, which is used as an index of glycemic variability), and standard deviation of blood glucose (SDBG), which reflects the amount of variation or dispersion of a series of glucose values.

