The multicenter design of this study enhances the generalizability and representativeness of the results. The change in HbA1c was used as the primary endpoint, as HbA1c reflects the patient’s blood glucose levels over the past 3–4 months and is considered the gold standard for blood glucose control. Therefore, the study endpoint reflects the effect of glycemic control. Additionally, CGM was employed as an exploratory study to assess glucose variability in more detail, offering deeper insights into future treatment strategies.

This study had several limitations. First, the open-label design may introduce a potential positive bias toward the FDC group, particularly concerning the DTSQ and ARMS-D scores, given the known convenience of a single tablet regimen. Second, the 24-week duration of the trial limited our ability to assess long-term outcomes, including the trajectory of β-cell function, sustainability of glycemic control, and more comprehensive safety profile. Third, the recruitment of participants exclusively from Chinese centers may limit the generalizability of our findings to other ethnic groups and healthcare settings. While this focus provides highly relevant data for the Chinese population, future multinational studies are warranted to confirm the global applicability of the results.

In conclusion, as the first study to directly compare the dapagliflozin/metformin XR FDC with the separate administration of dapagliflozin and metformin hydrochloride XR, this scientifically designed trial has the potential to provide crucial evidence supporting the use of FDCs. Additionally, it may offer valuable insights for physicians in selecting treatment regimens for diabetes and in improving patient adherence.

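### The per-protocol set leads the efficacy and patient-reported secondary comparisons, adherence included, where the randomised set should lead

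*Protocol article*

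**What the plan says.** All of this is in the Statistical analysis section (2.7) unless noted.

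- Lead set: "The secondary endpoints will be analyzed in the PPS".
- How the set is formed: "The per-protocol analysis set (PPS) will include patients without an important protocol deviation that might affect the primary efficacy analyses". The article gives neither a list of such deviations nor a compliance threshold.
- Role of the other set: "The analyses for the primary and secondary endpoints will be repeated using FAS to examine the robustness of the results". The FAS "included all randomized patients with documented baseline assessment and at least one post-baseline assessment for the primary efficacy endpoint".
- Adherence endpoint (section 2.3): "The differences in patient medication usage between the two groups were measured with adherence to refills and medications scale for diabetes (ARMS-D) at week 24".
- Test: "Differences in DTSQ and ARMS-D scores at week 24 between the two groups will be compared using the t-test or Wilcoxon rank-sum test". DQOL and the glucose changes use ANCOVA, and HbA1c below 7.0% uses logistic regression. None of these has a margin.
- The safety endpoints, which section 2.3 also lists as secondary, are analysed in the safety set.

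**The concern.** Adherence and satisfaction are named in the trial's title, and the Introduction motivates the study partly by the expectation that a single tablet improves adherence. For these questions the reader wants the contrast between the arms as randomised.

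A per-protocol lead can be argued for the HbA1c non-inferiority test, because protocol deviations tend to dilute a difference and so make non-inferiority easier to show. That argument does not carry over to a test of difference. Nor does a deviation that disturbs HbA1c give a reason to discard a patient's satisfaction, quality-of-life or adherence questionnaire.

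ARMS-D is the clearest case. Not taking the study drug is an obvious candidate for a deviation that affects HbA1c. If it counts, the patients removed are those whose poor adherence is being measured, and the arm that adheres worse loses more of them. For the other endpoints the selection is on a related post-randomisation variable, not on the outcome itself. At stake is the headline estimate for a named objective.

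**Working it through.** **The plan's own figures.** The article gives no figure for any secondary endpoint. The only one used here is 632 randomised 1:1, or 316 per arm. It comes from the primary calculation: n = 2 × (1.960 + 0.842)² × 1.2² / 0.3² = 251.2, so 252 per arm by the normal approximation. The t-based version gives power of 79.98% at 252 and 80.14% at 253, so 253. Then 2 × 253 / 0.8 = 632.5, against 632 stated. That calculation stands, and the choice of set does not affect it.

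**The sections side by side.** The PPS is defined by reference to the primary efficacy analysis and then reused for endpoints that are not HbA1c non-inferiority. Elsewhere the plan does otherwise: the CGM comparison, sized in section 2.6 as an exploratory superiority test, draws its patients from the FAS and not the PPS.

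**Illustration for adherence.** Every input below except 316 per arm is an assumption.

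- The adherence score A is normal with SD 1 and higher is better. Its mean is 0 under co-administration and 0.25 under FDC.
- Exclusion is decided on a compliance measure C (SD 1) that correlates ρ with A. Patients with C below a common cut-off c are dropped.
- c is set so that 10% or 20% of the co-administration arm is excluded: c = −1.2816 or −0.8416.

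With λ(x) = φ(x) / (1 − Φ(x)), the mean of A among retained patients is μ + ρλ(c − ρμ). So

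PPS difference = 0.25 + ρ[λ(c − 0.25ρ) − λ(c)].

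Example, ρ = 1 and 10% excluded: λ(−1.2816) = 0.1950 and λ(−1.5316) = 0.1317, so the difference is 0.25 + 0.1317 − 0.1950 = 0.187. That is 75% of 0.25.

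Power is Φ(difference / √(s₀²/n₀ + s₁²/n₁) − 1.96). Here n is 316 times the fraction retained and s² = 1 − ρ²λ(x)[λ(x) − x], with x the arm's cut-off (c or c − 0.25ρ). With all 316 per arm it is Φ(0.25 / √(2/316) − 1.96) = Φ(1.18) = 88%.

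| ρ | FDC arm excluded (co-administration 10% / 20%) | PPS difference, SD | Share of truth retained | Power |
|---|---|---|---|---|
| 0.3 | 8.7% / 18.0% | 0.244 / 0.241 | 98% / 96% | 84% / 79% |
| 0.5 | 8.0% / 16.7% | 0.233 / 0.225 | 93% / 90% | 82% / 77% |
| 0.8 | 6.9% / 14.9% | 0.208 / 0.188 | 83% / 75% | 78% / 70% |
| 1.0 | 6.3% / 13.7% | 0.187 / 0.155 | 75% / 62% | 74% / 62% |

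A simulation with one million patients per arm gives 97–98%, 90–93%, 75–82% and 63–75% retained, the same to within about one percentage point.

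**Direction.** Shrinkage towards zero follows from the common cut-off; it is not a general rule. Suppose exclusions track poor compliance only in the FDC arm (10% removed, ρ = 0.5) and are unrelated to adherence in the other arm. The PPS difference is then 0.25 + 0.5 × 0.1950 = 0.35, which is larger than the truth.

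**The case against.** Four points can be made for the plan.

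1. **The exclusion of poor adherers is not in the text.** This stands. A reader might infer that the PPS certainly removes them, but the article lists no deviations, and that list commonly sits in a fuller document. The ARMS-D mechanism is therefore conditional. That membership is settled after randomisation, by reference to HbA1c, is not conditional.
2. **The FAS analysis is pre-specified.** This stands too. A reader might infer that no randomised-set analysis is planned, and that would be wrong. No stated success criterion hangs on the secondary endpoints. The question is only which result leads, and the article does not say what governs if the two disagree.
3. **The bias may be small, and conservative for FDC.** In part. At weak correlation almost all of the difference survives, and under a common cut-off the estimate moves towards no difference. A reader might infer that about a third of the effect is lost, but that needs exclusion on the adherence score itself; ARMS-D is a questionnaire, and deviations would probably be judged on other records. Even the conservative case costs power, and the direction is not assured.
4. **The FAS is not all randomised patients.** Correct: it needs a post-baseline HbA1c. It is still much closer to the randomised comparison than a set chosen by deviations.

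Two neighbouring matters might be taken as part of the defect and are not. The Discussion already concedes that "the open-label design may introduce a potential positive bias toward the FDC group, particularly concerning the DTSQ and ARMS-D scores"; that is a limitation of open-label self-report under either set. And although "Drug dispensation and accountability" appears in Table 1, not making it an endpoint is a design choice, not an error.

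**Conclusion.** The point holds as a question of which set leads. For ARMS-D, DTSQ, DQOL, fasting and postprandial glucose and HbA1c below 7.0%, the plan puts a set selected after randomisation ahead of the FAS, and the non-inferiority rationale does not cover these comparisons. It does not extend to every secondary endpoint, as a reader might infer from the lead sentence: safety is analysed in the safety set. Selection on the outcome itself applies only to ARMS-D, and only if non-compliance is an important deviation.

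The document does not fix the size. Under the stated assumptions the loss for ARMS-D runs from about 2% to 38% of the true difference, with power of 62–84% against 88%; under other exclusion rules the bias could go the other way. No size was computed for the other endpoints. Because the FAS repeat is already planned, this is a worthwhile correction and not a fatal omission.

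**What to change.** In section 2.7, before database lock, make the FAS, analysed by randomised arm, the lead set for the efficacy and patient-reported secondary endpoints, and the PPS the supportive repeat. State beside it that the FAS requires at least one post-baseline HbA1c, and report how many randomised patients per arm that leaves out. The primary non-inferiority analysis and the safety analyses need no change on this account.

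The cost is an exchange of roles between two sentences. Both analyses are already planned, and no new data and no change of sample size are needed. Settling the order before lock also prevents a choice between conflicting results once they are known. A tablet-count adherence summary from the accountability records could be added, but it is optional.
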